## Abstract

**Background:**

Early childhood development (ECD) is essential in human capacity building and a critical element in the intergenerational process of human development. In some countries, social programs targeted at improving ECD have proven to be successful. Oaxaca is one of the States with the greatest social inequities in Mexico. Therefore, children in Oaxaca are at a high risk of suboptimal ECD. In 2014, the non-governmental organization (NGO) Un Kilo de Ayuda started to implement the Neurological and Psycho-affective Early Childhood Development Program in eighty marginalized communities of Oaxaca. In this article, we present the impact evaluation design to estimate the effect of this program on ECD.

**Methods:**

We will use a cluster randomized stepped-wedge design with an allocation ratio of 1:1. Communities will be randomly assigned to each study group: four groups of twenty communities each. We expect that children from intervened communities will show better ECD outcomes.

**Discussion:**

This study is one of the few rigorous assessments of the effect of an ECD program on the neurodevelopment of Mexican children recruited in their first 3 years of life from communities of high social vulnerability. Our study design is recommended when the way in which outcomes are measured and assessed depends on age, self-selection is present, and assignment is performed at an aggregate level. Implementation research will be conducted prior to study launch and quality control measures will be in place to maximize the fidelity of study design implementation.

**Trial registration:**

ClinicalTrials.gov NCT04210362

## Administrative information

Note: the numbers in curly brackets in this protocol refer to SPIRIT checklist item numbers. The order of the items has been modified to group similar items (see http://www.equator-network.org/reporting-guidelines/spirit-2013-statement-defining-standard-protocol-items-for-clinical-trials/).

## Background {6a}

Early childhood development (ECD) is essential in human capacity building and a critical element in the intergenerational process of human development [1]. ECD is multidimensional and influenced by many factors such as genetics, biological status (health and nutrition), the immediate environment (caregiving components), and community characteristics [2]. Sensitive and responsive nurturing care along with education and good nutritional health can improve ECD; however, the most sensitive window of opportunity to advancing ECD, including its social, emotional, and cognitive aspects, is narrow because the greatest developmental benefits and returns on investment are achieved when nurturing care is offered during gestation and the first 3 years of life [3, 4]. Suboptimal ECD affects not only the child, but also society’s social and economic development [5]. Failure to provide nurturing care in early life to the most vulnerable will lead to high subsequent costs due to excess mortality and morbidity as well as in reduced human capital productivity, perpetuating the vicious cycle that leads to ever increasing social and economic inequities [6].

Studies conducted across different countries have shown that social protection policies and programs have been successful at improving ECD. These interventions include childhood care education, promotion of maternal mental health and wellbeing, and conditional cash transfer programs [7, 8]. In Latin America, “Chile Crece Contigo” is an example of a successful multisectoral evidence-based large-scale program. Funded by the Chilean government and emerging from a national consensus in which the civil society participated, the program offers high-quality ECD information for families and healthcare providers among its various health and education benefits [8]. Another example of a large-scale program is “Cuna Mas” in Peru which consists of home visiting interventions aimed at improving parenting practices; it has showed a positive impact in developmental outcomes [9, 10]. In Colombia, Ecuador, and Mexico, existing cash transfer programs have been used to deliver ECD interventions [11]. Multiple studies across the globe, including Jamaica, Pakistan, and Turkey, have shown that incorporating nurturing care elements in interventions improved child development and later adult outcomes [7].

The most rigorous evaluations of ECD interventions have followed experimental designs which are considered the gold standard to estimate effects. Quasi-experimental designs may be used when randomization is not possible due to self-selection amd ethical or logistical considerations. Studies have found that in hard-to-reach communities with high levels of poverty, children live at risk of nutritional deficiencies and suboptimal levels of neurodevelopment [12]. Often governments face difficulties to reach these populations, many of which are geographically isolated. Therefore, non-governmental organizations (NGOs) are key for complementing and expanding the reach of governmental efforts seeking to improving ECD in the most socially isolated communities.

Located in the South of the country, Oaxaca is one of the States with the greatest social inequities in Mexico. In 2018, 66% of its population lived in poverty, and only 16% had access to health services and 27% had major gaps in the education system [13]. Hence, it is not surprising that Oaxaca has a life expectancy at birth lower than the national average [14] and that a large proportion of children may be at risk of suboptimal ECD. Since 1986, the NGO Un Kilo de Ayuda A. C. (UKA) has been involved in preventing child undernutrition in contexts of high poverty in Mexico. In 2014, UKA started to implement the Neurological and Psycho-affective Early Childhood Development Program (NPECDP-UKA) in eighty socially deprived communities of Oaxaca. This program seeks to improve levels of ECD on children from these communities and is one of the three programs constituting UKA’s Integral Model of Early Child Development. The other two programs focus on improving physical development of children and fostering community development, respectively.

Assessing ECD requires addressing serious methodological challenges given its multidimensional nature. Ethical matters are also important; for example, interventions that include already proved beneficial components must be offered to all groups in a research study limiting the possibility of randomization and inclusion of control groups without any intervention. Interventions designed to improve ECD also face logistical challenges, since they typically include more than one component and numerous instruments to assess all its dimensions [15–18]. Furthermore, they require interdisciplinary teams to deliver the interventions and to conduct unbiased assessments.

This paper aims to present the impact evaluation protocol to assess the effect of the NPECDP-UKA on ECD in preschool children from eighty high social deprived communities in Oaxaca, Mexico. The evaluation has the potential to visualize the effects of an educational intervention performed by an NGO on ECD. It represents an opportunity to assess the developmental lag in the studied communities as well as to provide elements for the continuation, expansion, or modification of the interventions. As part of the civil society and in coordination with authorities, UKA provides a channel to deliver ECD parenting education focused on responsive caregiving. Given the multiple aspects of nurturing care, it is important to have in place multisectoral interventions [19]. Along with the important role from the government, the private sector as well as the civil society can add coordinated contributions to improve and sustain ECD interventions.

The present protocol shows a novel way to assess the effects of an intervention on developmental outcomes where difference scores are not possible due to the age-specific nature of developmental scales. The proposed stepped-wedge experimental design overcome this difficulty and tackle different sources of biases from self-selection, cohort, and community effects. Additionally, the quasi-experimental component of the evaluation allows to study determinants of participation and controls for community and cohort effects. The design could be adapted and applied for studying any other outcome for which age-specific scales are used. Furthermore, it provides useful elements for designing future evaluations by making explicit important biases that may be at play.

To the best of our knowledge, this evaluation study and its design is the first effort of its kind applied to ECD outcomes in Mexico. We hypothesized that children from intervened communities will show better ECD outcomes.

## Methods

### Design and setting {9}

To assess the effect of NPECDP-UKA on ECD, we will use a cluster randomized stepped-wedge design [20] with an allocation ratio of 1:1. A total of 80 communities will be randomly assigned to four study groups using blocking. Each block will be comprised of four communities (twenty blocks in total) with a similar percentage of indigenous population, social marginality level, and urbanicity measured in the 2010 Census [21, 22]. Within each block, the four treatments will be randomly allocated to communities (each community receiving exactly one treatment).

For ethical reasons, interventions will not be allocated at the individual level. Instead, all study groups consist of communities in which eligible caregivers will be invited to enroll in the NPECDP-UKA, but the program will be deployed sequentially at the community level, according to the timing randomly assigned. This defines the distinctive characteristic between study groups, for example, whereas group A will have a total of 30 months of the exposure to the program at its last assessment; group D, the last study group to be incorporated, will have no exposure to the program during the study and will be measured only once (Table 1). In all study groups, a baseline assessment will be performed before implementing the intervention.

**Table 1 Tab1:**
[figure not shown]
Study groups, exposure times, and age of children

The main feature of the proposed design is the possibility of comparing groups of children at the same age range but with a different time of exposure to NPECDP-UKA, at the same calendar period. This design feature will allow to eliminate potential confounding cohort effects since children with the same age across study groups will also share the same year of birth. Table 1 shows the age range of children for each study group at different study calendar periods. The upper age limit of the ECD assessment will be 60 months; therefore, the first group of communities to be exposed to the program will include children aged 1–30 months at their first assessment and these children will be aged 31–60 at their final assessment. At given calendar periods (*t* = 2, 4, 6), the group unexposed to the intervention will function as a control group. For example, the last group of communities to be incorporated to the study (group D) will function as a control group at the last calendar period (*t* = 6). This will allow to estimate the effect of NPECDP-UKA on ECD for exposure times of 30 months (group A vs group D), 24 months (group B vs group D), and 12 months (group C vs group D). Given the rapid changes at early ages and considering the first thousand days of life as a critical opportunity window, we consider that the planned exposure times are adequate to detect changes as well as a gradient of the effect with respect to time exposure. Comparisons between groups will be performed cross-sectionally for children of the same age range. There will be a total of six calendar periods, with a time span of 6 months between the mid-point of consecutive periods and an approximate time span of 6 months between consecutive individual measurements.

In addition to the assessment of the effect of NPECDP-UKA on ECD through a cluster randomized stepped-wedge design, children from the initial communities (group A) but whose caregivers refuse to participate in the NPECDP-UKA and continue participating in the study measurements will be assessed at the same time as the intervened children for three consecutive measurements. This will allow to identify predictors of participation and approximate program effects through a quasi-experimental analysis after 6 and 12 months of intervention using propensity score matching techniques to adjust for self-selection predictors [23]. For outcome variables with well-defined changes (e.g., nutritional status indicators), a difference in difference estimator along with propensity score balancing will be used. Figure 1 shows a simplified version including both the cluster randomized stepped-wedge design and the quasi-experimental design. The former is shown just for the comparison between group B and group A in children aged 7 to 36 months at *t* = 2, where group B works as a control group.

**Fig. 1 Fig1:**
[figure not shown]
Simplified cluster randomized stepped-wedge and a quasi-experimental design

### Participants {10}

Communities were selected if they met the following inclusion criteria: located in municipalities where the NPECDP-UKA was not currently operating and with more than thirty-five inhabitants under 5 years, according to the census of 2010 [22]. Within selected communities, children will be included if they match the designed age range, and their caregivers agree to participate in the study. One of the children’s parents or legal caregiver will be asked to sign the study’s consent form by UKA staff (details mentioned below, in the recruitment section). Children’s blood samples will be obtained from capillary blood samples by trained personnel to assess their anemia status. One of the children’s parents or legal caregivers will be asked to sign an additional consent form prior to blood collection. Children whose parents or legal caregivers refuse to provide consent for blood sample collection will not be excluded from the study since the outcomes of interest do not require analysis of blood samples.

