### Participant timeline {13}

Table 2 shows the chronogram of study activities including intervention implementation schedule across study groups and the corresponding measurements of ECD and nutritional status outcomes among pregnant women and children. The number of repeated measurements across time will depend on the timing when each group starts being exposed to the intervention.

**Table 2 Tab2:** Chronogram of study activities and measurements of child development scales

Activities	Study calendar period						
	t0	t1	t2	t3	t4	t5	t6
Community’s allocation	X						
Eligibility in communities A		X					
Enrollment in communities A		X					
Measurement in communities A*		X	X	X	X	X	X
Eligibility in communities B			X				
Enrollment in communities B			X				
Measurement in communities B*			X	X	X	X	X
Eligibility in communities C					X		
Enrollment in communities C					X		
Measurement in communities C*					X	X	X
Eligibility in communities D							X
Measurement in communities D							X
Measurement of CDE-II		X	X	X	X	X	X
Measurement of MSCA							X
Measurement of BSID-III		X	X	X			
Nutritional status assessment		X	X	X	X	X	X

*Intervention starts right after their first measurement. There will be a time span of 6 months between the mid-point of consecutive periods and an approximate time span of 6 months between consecutive individual measurements

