### Sample size {14}

Our main outcome statistic is the proportion of children with developmental lag (yellow category) or at risk of development delay (red category). The effect will be assessed comparing these proportions between the exposed groups and the unexposed group.

Sample sizes were planned so that there are approximately 150 children for each 6-month age interval; this approximates a uniform distribution of observations across age groups and study groups for the relevant age ranges. As mentioned before, given the stepped-wedge design of the study, groups will be incorporated sequentially but comparisons between study groups will be performed at the same study calendar period and for children at the same age interval (see Table 1 for a representation of the stepped-wedge design). Group A will include 1–30-month-old children (*n* = 750); these children will be 31–60 months old at their final measurement and compared to children with the same ages in group D (*n* = 750). This will allow to assess the effect of NPECDP-UKA on ECD after an exposure time of 30 months. Other comparisons are possible. For example, ECD outcomes from group B vs group D (*n* = 900) and group C vs group D (*n* = 1200) at the final study calendar period (Table 1). Table 3 shows the effect size in terms of a difference of proportions given different levels of proportions in the unexposed group (group D), different design effects (DEFF) that consider that measurements in the same community are correlated (DEFF = 1.5, 2.0) [31], a significance level of 0.05 under a bilateral test, and a statistical power of 80.0%.

**Table 3 Tab3:** Sample sizes and effect sizes in terms of a difference of proportions between two groups given a statistical power of 80%

Sample size per group	Proportion in the group without exposure to NPECDP-UKA	Effect size (difference of proportions) given different design effects (DEFF)*		
		DEFF = 1.0	DEFF = 1.5	DEFF = 2.0
750	0.50	0.072	0.088	0.102
900	0.50	0.066	0.081	0.093
1200	0.50	0.057	0.070	0.081
750	0.25	0.065	0.080	0.093
900	0.25	0.059	0.073	0.085
1200	0.25	0.051	0.063	0.073
750	0.125	0.052	0.064	0.075
900	0.125	0.047	0.058	0.068
1200	0.125	0.040	0.050	0.058

*The design effect is a factor that when multiplied by the variance of an estimator under a simple random sampling design corresponds to its variance under a complex sampling design; in this case, a design with clustering of observations within communities

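### Families who move in between the exposed group's enrolment and the control group's assessment can enter only the control side of each contrast

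*Protocol article*

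**What the plan says.** The entry rule in Participants {10} has two parts, age and consent: "children will be included if they match the designed age range, and their caregivers agree to participate in the study". Recruitment {15} adds a public meeting and a house-to-house stage that looks for children of the right age at that time. Neither section states how long a child must have lived in the community.

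The exposed groups are followed cohorts. Group A "will include children aged 1–30 months at their first assessment and these children will be aged 31–60 at their final assessment". Table 2 marks eligibility once per group, at t1 for A, t2 for B and t4 for C, with the note "Intervention starts right after their first measurement". No later top-up is described.

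Controls are found later. At t = 2, 4 and 6, "the group unexposed to the intervention will function as a control group". In Table 2 the row "Eligibility in communities D" is marked at t6 only, and Design and setting {9} says that group D "will have no exposure to the program during the study and will be measured only once". Sample size {14} describes the longest contrast from group A's side: "these children will be 31–60 months old at their final measurement and compared to children with the same ages in group D".

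The section on data collection lists many household and maternal characteristics, but neither date of arrival nor length of residence. Statistical methods {20a, 20b, 20c} provides regression adjustment if observed characteristics are unbalanced. The Discussion names cohort, community, self-selection, aging and period effects as the main biases. It does not mention migration.

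**The concern.** The two sides of a contrast are drawn from the same kind of community at different times. A child analysed in group A at t6 was in an A community at t1. A child of the same age in group D need only be in a D community at t6. The control side is therefore residents plus later arrivals, and the exposed side has no such arrivals.

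Randomisation balances the communities, but the difference comes from the time of entry, which differs by arm after allocation. The Discussion's argument that all subjects choose to take up the programme concerns willingness, not date of arrival.

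If newcomers and residents differ in development, part of that difference is read as a programme effect. The window also lengthens with the exposure being studied, so the bias can disturb the exposure gradient that the design is meant to show. If arrival dates are not collected, no later analysis can separate the newcomers.

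**Working it through.** **1. Could births explain the difference?** No. Children in D aged 31–60 months at t6 were 1–30 months old at t1, 30 months earlier, so all were already born when A was enrolled. The planned sizes allow the same check for the other contrasts at 150 children per 6-month age interval:
- B–D: 900/150 = 6 intervals, 36 months of age, so 25–60 months at t6 and 1–36 months at t2.
- C–D: 1200/150 = 8 intervals, 48 months of age, so 13–60 months at t6 and 1–48 months at t4.

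What differs is arrival, not birth.

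**2. Length of the window.** Periods are 6 months apart, so the window is 6 × (control period − comparator's enrolment period):

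| Contrast | Periods | Window |
|---|---|---|
| A–B | t1 to t2 | 6 months |
| A–C | t1 to t4 | 18 months |
| A–D | t1 to t6 | 30 months |
| B–D | t2 to t6 | 24 months |
| C–D | t4 to t6 | 12 months |

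The last three match the article's own exposure times: "30 months (group A vs group D), 24 months (group B vs group D), and 12 months (group C vs group D".

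**3. The plan's own figure.** Table 3 gives 0.080 for 750 per group, control proportion 0.25 and design effect 1.5. Take a two-sided 0.05 test, 80% power and pooled variance, with the effect added to the control proportion (0.25 against 0.33, mean 0.29):

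n = [1.960 × √(2 × 0.29 × 0.71) + 0.842 × √(0.25 × 0.75 + 0.33 × 0.67)]² / 0.080² ≈ 504, and 504 × 1.5 = 756, against the stated 750.

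Table 3 reproduces and is not in question.

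**4. Size of the bias.** Let m be the share of newcomers among controls and δ the newcomer-minus-resident difference in the yellow/red proportion. The control proportion is then the residents' proportion plus mδ, so the exposed-minus-control difference shifts by −mδ. The documents give neither quantity. Both ranges below are assumptions.

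| m | δ = 0.05 | δ = 0.10 | δ = 0.20 |
|---|---|---|---|
| 5% | 0.0025 | 0.005 | 0.01 |
| 10% | 0.005 | 0.01 | 0.02 |
| 20% | 0.01 | 0.02 | 0.04 |

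The sign follows δ, which could be positive or negative.

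**5. Effect on the test when the programme does nothing.** SE = √(0.1875 × 1.5 × 2/750) = 0.0274. The rejection rate is 1 − Φ(1.96 − b/SE) + Φ(−1.96 − b/SE):

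| Bias b | Two-sided error |
|---|---|
| 0.0025 | about 5.1% |
| 0.01 | about 6.5% |
| 0.02 | about 11% |
| 0.04 | about 31% |

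At design effect 2.0, SE = √(0.1875 × 2 × 2/750) = 0.0316, and biases of 0.02 and 0.04 give about 10% and 24%.

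**6. If the bias masks an effect.** At control proportion 0.50, design effect 2.0 and a true reduction of 0.102, a bias of 0.01 lowers power from 0.80 to about 0.72.

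**The case against.** The strongest reply is that this is a condensed article. It says that a full protocol exists, and a residence definition is the kind of operational detail that may sit there. No sentence says that recent arrivals count as controls. This stands as a caution: if the full protocol has such a rule, it is enough to state it. It does not dispose of the point, because the article itself gives the entry rule, the timing of eligibility and the list of data collected, and together these produce the asymmetry.

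Second, the size is unknown. The article describes populations in such settings as often geographically isolated, which does not suggest heavy in-migration. At 3% newcomers, even a gap of 0.20 gives a bias of 0.006 and an error of about 5.5%. This stands.

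Third, covariates are collected and may be adjusted for. A newcomer–resident gap that works through assets, education or maternal characteristics would be reduced. Any part tied to residence itself would remain, so a reader should not infer that the whole gap passes into the estimate.

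Two stronger readings also fail. One is that only controls contain recent in-migrants. Groups A–C may include families who arrived shortly before their own enrolment, and only arrivals after that point are one-sided. The other is that the bias would imitate a dose-response. It could equally mask one, since its sign is unknown. A steady rise with exposure also needs steady inflow and a gap that does not fade with time in the community.

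**Conclusion.** The asymmetry follows from the stated entry rule and timetable, and nothing in the article removes it. Its size and direction cannot be determined from the document. Under the assumed ranges the bias runs from 0.0025 to 0.04, that is, from about 3% to 50% of the 0.080 detectable difference. The middle case of 0.01 is modest, with error of about 6.5%. The 31% figure needs the largest share and the largest gap together and should not be taken as the expected consequence. The documents do not support a claim that the results will be seriously biased, or biased in the programme's favour.

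Two assumptions lie behind this: that groups A–C are not topped up with later arrivals, and that families who leave are lost about equally from both sides. The article does not say whether children who move away are traced. The point merits correction mainly because the information needed is cheap to collect and cannot be recovered if it is not collected.

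**What to change.** Add the child's date of arrival in the community to the household questionnaire for all groups. Where a group's baseline has already been taken, ask at the next measurement.

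For each contrast, estimate the effect among control children already resident at the exposed comparator's enrolment period: t1 for contrasts with A, t2 for B–D and t4 for C–D. Report the estimate with newcomers included alongside it, and state the newcomer share for each contrast.

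The data cost is one question. The statistical cost is that the control sample shrinks by the newcomer share. At 20%, D falls from 750 to 600, and the detectable difference grows by √[(1/750 + 1/600)/(2/750)] = √1.125 = 1.06, from 0.080 to about 0.085. At 3% the growth is below 1%. The cost is thus largest where the newcomer share is largest.

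The restriction matches the groups on residence only. It does not address loss to follow-up in the exposed cohorts, whose children must also have stayed in the study until the comparison.
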